## 8.5 Participant Withdrawal and Changes of Status Within Trial

Informed consent is defined as the process of learning the key facts about a clinical trial before deciding whether to participate.

Parents/guardians should be aware at the beginning of the process that they can freely withdraw (discontinue participation of) the participant from the trial at any time. A parent/guardian who withdraws their child from the trial does so completely (i.e. from trial treatment and all follow up) and is not willing to have any of their subsequent data used in any future trial analysis. If a child is randomised but subsequently withdrawn prior to surgery, the child will not receive the trial intervention and therefore there will be no outcome data to be collected for them. However, where appropriate, these patients will still be reported in the formal analyses, such as in the consort flow diagram.

A parent/guardian who wishes to end their child's participation in a particular aspect of the trial, will be considered as having changed their status within the trial.

The changes in status within the trial are categorised in the following ways:

- No trial related follow-up: The parent/guardian would no longer like the participant to undergo trial assessments in accordance with the protocol schedule but is willing for routine data to be collected from standard follow-up and if applicable using any central UK NHS bodies for long-term outcomes (i.e. the participant's data can be collected at standard assessments and used in the trial analysis, including data collected as part of long-term outcomes).
- No biopsy sub-study: The parent/guardian would no longer like the participant to take part in the biopsy sub-study. If this occurs prior to surgery, no study biopsies will be taken during the procedure; if it occurs after surgery, the investigator will confirm whether any biopsies already obtained can be kept and analysed.
- No genetic sub-study: The parent/guardian would no longer like the participant to take part in the genetic sub-study. If this occurs prior to surgery, no blood sample for genetic analysis will be taken prior to the procedure; if it occurs after surgery, the investigator will confirm whether any blood already obtained can be kept and analysed.

A patient may also be withdrawn from the trial prior to their index operation for clinical reasons e.g. change of operation not requiring cardioplegia. The details of either withdrawal or change of status within the trial (date, reason, and category of status change) should be clearly documented in the source data and on the Trial Exit/Change of Status CRF .

Patients found to be ineligible post randomisation should be followed up according to all trial processes and will still have their data analysed unless they explicitly change their level of participation.

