#### 6.2.2 Blinding

As the technique for delivery of cardioplegia and interval between doses necessarily differs between treatment groups, patient safety may be compromised by blinding those administering the cardioplegia. The operating surgeon, perfusionist, anaesthetist, theatre scrub team and research nurse therefore will *not* be blinded to the intervention.

However, as the cardioplegia is only administered during surgery, patients, parents/guardians, and outcome assessors such as cardiologists, other surgeons, PICU medical and nursing staff, and ward staff will be blinded to the allocation. This will be maintained by only documenting the use of cardioplegia in the medical notes without referring to which product was used.

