### 13.2 Analysis of Outcome Measures

A separate Statistical Analysis Plan will be produced and will provide a more comprehensive description of the planned statistical analyses. A brief outline of these analyses is given below. The primary comparison groups will be composed of those treated with del Nido cardioplegia versus those treated with St. Thomas' blood cardioplegia. In the first instance, all analyses will be based on the intention to treat principle, i.e. all participants will be analysed in the treatment group to which they were randomised irrespective of compliance or other protocol deviation. For all outcome measures, appropriate summary statistics will be presented by group (e.g. proportions/percentages, mean/standard deviation, or median/interquartile range).

Intervention effects will be adjusted for the minimisation variables listed in section 6.2.1 where possible. No adjustment for multiple comparisons will be made.

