### 13.2.4 Missing Data and Sensitivity Analyses

Every attempt will be made to collect full follow-up data on all study participants; it is thus anticipated that missing data will be minimal, especially given the short duration of follow-up. Randomised participants who do not undergo surgery cannot contribute data to the primary outcome and will therefore be excluded from the primary analysis. Additional participants may be randomised to ensure the sample size is maintained. Participants who undergo surgery but have missing primary outcome data for troponin at one or more timepoints after aortic cross-clamp release will not be included in the primary analysis in the first instance. This presents a risk of bias, and sensitivity analyses may be undertaken to assess the possible impact of the risk. Full details of all sensitivity analyses will be included in the Statistical Analysis Plan.

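### Section 8.5 stops outcome collection for every child withdrawn before surgery, including any withdrawn by the clinical team who still have a cross-clamped operation and so have outcomes to measure

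*Protocol*

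**What the plan says.** Protocol Section 8.5 covers departures before surgery in several places.

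- **Parental withdrawal** is complete: the parent "is not willing to have any of their subsequent data used in any future trial analysis". A lesser status is open to a parent who "is willing for routine data to be collected from standard follow-up".
- **Any child withdrawn after randomisation and before surgery**: "the child will not receive the trial intervention and therefore there will be no outcome data to be collected for them". Such children are reported where appropriate, with the CONSORT diagram as the example.
- **Clinical withdrawal**: "A patient may also be withdrawn from the trial prior to their index operation for clinical reasons e.g. change of operation not requiring cardioplegia". Date, reason and category must be documented.
- **Ineligibility discovered late**: "Patients found to be ineligible post randomisation should be followed up according to all trial processes and will still have their data analysed", unless the level of participation is explicitly changed.

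Section 13.2 sets the analysis principle: "all participants will be analysed in the treatment group to which they were randomised irrespective of compliance or other protocol deviation". The same section defines the comparison groups by the treatment received. Section 13.2.4 says "Randomised participants who do not undergo surgery cannot contribute data to the primary outcome and will therefore be excluded from the primary analysis", and allows further participants to be randomised to keep up the sample size.

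On who knows the arm, Section 6.2.2 says "The operating surgeon, perfusionist, anaesthetist, theatre scrub team and research nurse therefore will *not* be blinded to the intervention". Parents are blinded. Randomisation is pre-operative (Table 3 in Section 8.4).

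**The concern.** Section 8.5 reasons from the trial product not being given to there being no outcome to collect. The outcomes do not depend on which product was used. Troponin AUC is timed from cross-clamp release, ventilation from the end of bypass, intensive care stay from admission, and hospital stay from the day of surgery (Sections 8.1 and 8.2). A child withdrawn by the team who then has a cross-clamped operation with another cardioplegia has all of these.

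Two things are at stake. First, the intention-to-treat promise in Section 13.2 cannot be kept for such a child, because the data were never collected. Troponin samples fall due within 24 hours of clamp release, so an analysis plan cannot recover them. Second, clinical withdrawal is open to staff who are not blinded, and replacement restores the numbers but not the comparability. That leaves a route by which exclusion could depend on the allocated arm.

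**Working it through.** **1. The rules side by side.** Consider a randomised child whom the team withdraws before surgery for a clinical reason and who is then operated on with cross-clamping.

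| Rule | Consequence for this child |
|---|---|
| 8.5, withdrawn before surgery | No outcome data collected |
| 8.5, found ineligible after randomisation | Followed up and analysed |
| 13.2, intention to treat | Analysed as randomised |
| 13.2.4, no surgery | Does not apply: the child has surgery |
| 13.2.4, missing post-clamp troponin | Left out of the primary analysis, because samples were not taken |

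The first rule contradicts the second and third. The last shows how the loss arises: non-collection under 8.5 becomes missing data under 13.2.4.

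**2. The overlap is a practical one.** Section 4.2 excludes a predicted clamp time under 30 minutes, at the surgeon's discretion. If that prediction is revised after allocation, the child could be classed as withdrawn for clinical reasons (no data) or as ineligible (analysed). Section 8.5 does not say which applies.

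**3. The plan's own figure.** Section 13.1 gives a difference of 19.2 µg.h/L, SD 42.0, 90% power and type I error 0.05 (taken as two-sided). The two-sample t-test gives 101.5, so 102 per group and 204 in total, as stated.

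**4. Size of a possible bias.** The inputs not in the protocol are assumptions:

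- a share p of one arm only is removed;
- those children's mean AUC lies a distance d from their arm's mean;
- 102 per arm are still analysed, since replacement is allowed;
- the SD is unchanged and there is no true effect.

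SE of the difference = 42 × √(2/102) = 5.88 µg.h/L.

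Shift in that arm's mean = p × d / (1 − p).

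Error rate = P(Z > 1.96 − shift/SE) + P(Z < −1.96 − shift/SE).

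| p | Shift, d = 21 (0.5 SD) | Error rate | Shift, d = 42 (1 SD) | Error rate |
|---|---|---|---|---|
| 3% | 0.65 | 5.1% | 1.30 | 5.6% |
| 5% | 1.11 | 5.4% | 2.21 | 6.6% |
| 10% | 2.33 | 6.8% | 4.67 | 12.5% |

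For p = 3% and d = 42: 0.03 × 42 / 0.97 = 1.30, which is 1.30/19.2 = 7% of the target difference.

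**5. Cross-check by simulation.** The settings were log-normal AUC with mean 64 and SD 42, 110 per arm, no true effect, and removals from one arm without replacement. Removing 3 children at random from the top third shifts the difference by about 1.3 µg.h/L and gives an error rate of 5.6%, in line with the formula. Removing exactly the 3 highest values gives 13.5%, but that needs foresight that nobody has before surgery.

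**The case against.** The strongest reply is that the group is narrow.

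- **Parental withdrawal.** The sentence follows directly on the rule for parents. Where a parent refuses use of later data, the absence of outcomes follows from consent and is not a design fault. Parents are blinded, so their decisions should not depend on the arm. This stands.
- **The only clinical example.** An operation without cardioplegia will ordinarily have no clamp release from which to time the primary outcome. This stands for the example, but the list of reasons is left open.
- **Non-receipt without withdrawal.** A child who is simply given another product and not withdrawn is already covered by Section 13.2. This stands, so no new parental status category is needed.
- **Motive.** Section 1.1.4 reports that 5 surgeons (17%) had concerns about del Nido with short clamp times. It also reports that 29 (91%) would use it in a trial, and predicted short clamp times are an exclusion. Section 6.2.5 does not describe what the confirmatory e-mail contains. That the surgeon deciding on withdrawal knows the arm in time is plausible but not stated.

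A reader might go further and infer that most children withdrawn before surgery go on to cardioplegic surgery, or that the team has a general right to remove children and so defeat intention to treat. The documents support neither. No section says how many withdrawn children are later operated on, and the text describes a permitted route, not its use.

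None of these replies repairs the inference in Section 8.5 or reconciles it with Sections 13.2 and 13.2.4.

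**Conclusion.** The point holds for one subset: children withdrawn by the clinical team who still have a cross-clamped operation. For them Section 8.5 discards measurable outcomes, goes beyond the exclusion in Section 13.2.4, contradicts Section 13.2 and overlaps with the rule on ineligibility. The possibility of exclusion that depends on the arm is a risk the wording leaves open, not something the protocol shows.

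The likely size is small. If a share equal to the planned 3% drop-out all fell in one arm, the error rate would stay at about 5.1% to 5.6%. Reaching 12.5% would need 10% one-sided removal at 1 SD. All these figures rest on assumed shares and offsets, and the direction of bias depends on which children leave. The case for changing the text is that the contradiction is clear and the remedy is cheap, not that a large bias is expected.

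**What to change.** In Section 8.5, replace the single sentence with three cases, taken in this order:

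- **(a) The parent refuses use of data.** No further data are collected.
- **(b) No index operation with aortic cross-clamping.** There is no primary outcome. The child is reported in the CONSORT diagram by arm, with the reason.
- **(c) An operation with cross-clamping takes place, but the allocated product is not given or the child is found ineligible.** The child stays in follow-up. All outcomes are collected and analysed as randomised, where consent stands.

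Use the same wording in Section 13.2.4, so that exclusion for having no operation means case (b) and nothing wider. In Section 13.2, define the comparison groups by randomisation instead of by treatment received.

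The cost is protocol wording. No sample-size figure changes. The downside is slight dilution of the contrast from a few children who did not receive the allocated product. Which product a child receives remains a clinical decision; only follow-up and analysis change.

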## 9 ADVERSE EVENT REPORTING

### 9.1 Definitions

The **Table 4** shows adverse event classification:

|                                               |              |                                                                                                                                                                                                                                                                                                                                                                                                                                                              |
|-----------------------------------------------|--------------|--------------------------------------------------------------------------------------------------------------------------------------------------------------------------------------------------------------------------------------------------------------------------------------------------------------------------------------------------------------------------------------------------------------------------------------------------------------|
| Adverse Event                                 | AE    | Any untoward medical occurrence in a participant or clinical trial subject administered a medicinal product and which does not necessarily have a causal relationship with this treatment.                                                                                                                                                                                                                                                                   |
| Adverse Reaction                              | AR    | All untoward and unintended responses to an IMP related to any dose administered.                                                                                                                                                                                                                                                                                                                                                                            |
| Serious Adverse Event                         | SAE   | Any untoward medical occurrence or effect that: 
 
• Results in death or is life-threatening
 
• Requires hospitalisation or prolongation of existing hospitalisation
 
• Results in persistent or significant disability or incapacity
 
• Is a congenital anomaly/birth defect
 
• Or is otherwise considered medically significant by the Investigator
 
 |
| Serious Adverse Reaction                      | SAR   | An Adverse Reaction which also meets the definition of a Serious Adverse Event                                                                                                                                                                                                                                                                                                                                                                               |
| Unexpected Adverse Reaction                   | UAR   | An AR, the nature or severity of which is not consistent with the applicable product information (e.g. Investigator Brochure for an unapproved IMP or (compendium of) Summary of Product Characteristics (SPC) for a licensed product). When the outcome of an AR is not consistent with the applicable product information the AR should be considered unexpected.                                                                                          |
| Suspected Unexpected Serious Adverse Reaction | SUSAR | A SAR that is unexpected i.e. the nature, or severity of the event is not consistent with the applicable product information. A SUSAR should meet the definition of an AR, UAR and SAR.                                                                                                                                                                                                                                                                      |

**Table 4.** Definitions of types of adverse events.

 The term life-threatening is defined as diseases or conditions where the likelihood of death is high unless the course of the disease is interrupted.

 Medical events that may not be immediately life-threatening or result in death or hospitalisation but may jeopardise the patient or may require intervention to prevent one of the other outcomes listed in the definitions above.

## 9.2 Adverse Events - General Recording Requirements

The collection and reporting of Adverse Events (AEs) will be in accordance with the UK Policy Framework for Health & Social Care (2017), the requirements of the Health Research Authority (HRA), and the sponsor's Code of Practice for Research. Definitions of the different types of AEs are listed in table of definitions, section 9.1.

It is routine practice to record adverse events in the patient's medical notes and it is also recommended that this includes the documentation of the assessment of severity and seriousness, and for causality (relatedness) in relation to the intervention(s) in accordance with the protocol. The assessment of causality should be made with regards to the Reference Safety Information (RSI). For the purposes of the DESTINY trial, this will be the Investigator Brochure for del Nido cardioplegia and the Summary of Product Characteristics for St Thomas' cardioplegia.

## 9.3 Adverse Event Reporting in DESTINY

The safety profile for this trial population and interventions are well established so although it is recommended that the severity, seriousness, and causality of all AEs should be recorded in the source data, a strategy of targeted reporting of AEs will therefore not affect the safety of participants. The reporting of only a subset of AEs via the Postoperative CRF, from the commencement of protocol defined treatment until 30 days, is consistent with aims of the trial.

## 9.4 Serious Adverse Event (SAE) Reporting in DESTINY

SAE reporting using standard definitions and practices for adult drug trials are not appropriate for clinical trials involving cardiac surgery in children [44] as events typically classified as SAEs occur commonly in the usual perioperative course for these children; their use would lead to a significant reporting burden and may detract from those events which are considered critical. A recent multi-centre UK study has defined important early morbidities associated with paediatric cardiac surgery as part of a wider study on morbidity in these patients [3], which have been adopted by the UK National Congenital Heart Disease Audit [45]. We therefore will use or adapt these definitions of important morbidities as the basis for expedited reporting of SAEs in this trial of children of all ages undergoing non-emergency cardiac surgery.

As the period of data collection lasts for 30 days, participants will remain under follow-up at the same hospital for the duration of their participation in the trial such that the local research team will collect all trial data on all events meeting the definition of SAEs directly. If the patient has been discharged home within 30 days, the occurrence of any SAE within this timeframe will be ascertained either during a routine follow-up clinic visit or by a telephone call.

## 9.5 SAEs not requiring expedited reporting to BCTU

Where the safety profile is well established, the causal relationship between either the intervention (or the participant's condition), and the SAE, may be known. That is, such events are protocol-defined as 'expected', will be considered as complications rather than adverse events if they occur within 30 days of the index operation, and will be recorded on the Postoperative CRF. This list is categorised by organ system, adapted from that used in the Pediatric Heart Network's Single Ventricle Reconstruction trial [46] and informed by the definitions developed during the Cardiac Morbidity study [3].

### *Cardiovascular*

- Arrhythmia, requiring medication or other treatment, excluding electrolyte supplementation
- Impaired cardiac function: Vasoactive Inotrope Score  $\geq 15$  at 48 hours after the index operation [1]

- Repeat aortic cross-clamp, unplanned during index operation
- Pericardial effusion or collection, requiring drainage
- Superior or inferior vena caval obstruction
- Other thrombosis or thromboembolism, demonstrated on imaging
- Other cardiovascular not requiring expedited reporting

#### *Respiratory*

- Chylothorax requiring intervention, whether drainage, dietary or medication
- Haemothorax, pleural effusion or pneumothorax, requiring drainage
- Hypoxaemia, requiring unplanned escalation of care
- Intubation for >2 weeks after the index operation
- Prolonged pleural effusion, requiring drainage for >10 days after the index operation
- Reintubation, any cause
- Other respiratory, including tracheal injury, vocal cord injury, or airway obstruction requiring intervention

#### *Neurological*

- Any new neurological deficit persisting at hospital discharge
- Other neurological not requiring expedited reporting

#### *Renal*

- Renal replacement therapy: peritoneal dialysis or haemofiltration for renal failure (oligo-anuria of <0.5ml/kg/hr and elevated creatinine for age) and/or fluid overload, initiated as a new support within 30 days after the index operation. Excludes renal support on ECLS [3].

